**Methods and design:**

The LABOR trial is a multicenter, prospective, two-arm, single-blinded, randomized trial. Patients of more than 60 years of age with a defect of less than 10 cm at its greatest diameter will be randomly submitted to open Rives or laparoscopic defect repair. All the participating patients will have a preoperative evaluation of their abdominal wall strength and mobility along with volumetry, respiratory function test, intraabdominal pressure and quality of life assessment.

The primary outcome will be the difference in abdominal wall strength as measured by a double leg-lowering test performed at 12 months postoperatively. The secondary outcomes will be the rate of recurrence and changes in baseline abdominal mobility, respiratory function tests, intraabdominal pressure, CT volumetry and quality of life at 6 and 12 months postoperatively.

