### Aim of the study

The aim of this study is to define the role of anatomical reconstruction and simple defect bridging in the mesh repair of incisional and primary ventral hernias. We wanted to analyze in depth whether defect bridging is comparable to anatomical reconstruction with mesh in terms of the strength of the abdominal wall as expressed by the differences among groups 1 year postoperatively in the grades of leg extension over the trunk during a DLL test.

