## Design

LABOR is a randomized, controlled, non-inferiority trial. Patients will be randomly allocated to receive a mesh repair of their incisional hernia with either laparoscopic bridging or open anatomical reconstruction. The trial has been registered on Current Controlled Trials as ISRCTN93729016.

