### Sample size calculation, randomization and statistical analysis

On the basis of a previous published work, the minimum DLL to define the non-inferiority of laparoscopic bridging vs. anatomic open reconstruction will be set to 5 degrees with a standard deviation of 8.5 degrees. With this hypothesis and for a power of 90% and an alpha of 5%, we will need 50 patients in each arm (total 100). If we consider a possible dropout rate of 10%, a total of 110 patients would be sufficient. As a consequence, approximately 20 patients for each center will be required.

A centralized block randomization stratified for center will be performed by a statistician not involved in patient management. Blocks will have a variable dimension (random) between 4 and 12 units. A total of five blocks will be obtained for each center in the event that the investigator continues enrollment beyond the initially planned sample size. The local investigators, after obtaining written informed consent of patients, will receive the randomization arm from the statistical center for each patient, then the patient will be allocated to the treatment group as indicated.

Data analysis will be performed by a statistician not involved in data collection at the main investigation center (University of Genoa). The means and standard deviations or medians with ranges, if asymmetry of data is detected, will be reported for all continuous demographic and clinical characteristics recorded, whereas counts and percentages will be recorded for categorical characteristics (e.g., gender, functional status and smoking habits).

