To compare the DLL test results during follow-up between the two groups of treatment, ANOVA for repeated measures will be adopted using DLL as the dependent variable. Because the DLL test cannot have a normal distribution, a ranking transformation will eventually be used. The same approach will be used for the other ordinal characteristics used as secondary outcomes (VAS as scoring for pain and AWS score) and, in general, for all other outcomes considered. If a consistent number of missing values is detected during the follow-up, ANOVA for repeated measures will be replaced by linear mixed or generalized estimating equation (GEE) models, which permit the exclusion of the data only from a single missing observation and not from the patient on overall as with ANOVA. Single comparisons between baseline values and each time during follow-up will be assessed using Bonferroni correction for multiple comparisons. All analyses will be performed on an intention-to-treat basis. A *p*-value lower than 0.05 will be considered statistically significant. SPSS (v.20, IBM Corp., Armonk, NY, USA) will be used for the statistical analyses.

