### Outcomes

#### Primary outcome

Changes in baseline DLL measures at 12 months postoperatively in both groups.

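### The analysis section does not name the 12-month between-arm DLL difference as the primary test, although the outcome definition and the sample size rest on that one contrast

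*Protocol article*

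**What the plan says.** The protocol article words the primary outcome in two ways.

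- **Value at 12 months.** The abstract (Methods and design) gives "the difference in abdominal wall strength as measured by a double leg-lowering test performed at 12 months postoperatively". The Aim of the study gives "differences among groups 1 year postoperatively in the grades of leg extension over the trunk during a DLL test".
- **Change from baseline.** The Primary outcome section gives "Changes in baseline DLL measures at 12 months postoperatively in both groups".

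DLL is measured before surgery and at 1, 6 and 12 months. The Secondary outcome section lists the 1- and 6-month DLL differences, so these are not primary.

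The Design section states "LABOR is a randomized, controlled, non-inferiority trial". In the sample size section the DLL threshold for non-inferiority "will be set to 5 degrees with a standard deviation of 8.5 degrees"; with 90% power and 5% alpha this leads to 50 per arm. The section does not say whether the SD belongs to the 12-month value or to the change, or whether alpha is one- or two-sided.

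For the analysis, the same section says that, to compare the arms during follow-up, "ANOVA for repeated measures will be adopted using DLL as the dependent variable". It adds: "Single comparisons between baseline values and each time during follow-up will be assessed using Bonferroni correction for multiple comparisons". If many values are missing, a linear mixed or GEE model replaces the ANOVA. No between-arm contrast at 12 months is named for either approach.

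**The concern.** A repeated-measures ANOVA with a group factor offers two tests that involve treatment. The group main effect is the difference between arms averaged over the visits in the model. If baseline is one of those visits, the average includes a time at which randomised arms are equal in expectation. The group-by-time interaction asks whether the arms diverge at any visit. Neither is the 12-month difference for which the 5-degree margin and the 50 per arm were set. The named follow-up tests compare times, not arms.

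This matters because the Clinical implications section reads an absence of difference as support for laparoscopic bridging. If the averaged effect were taken as the primary result, a late deficit could be diluted and the outcome would favour the trial's own hypothesis. If the interaction were taken, an early and transient difference could decide a question about 12 months. The choice would be made after the data are in.

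**Working it through.** **Inputs from the article:** margin 5 degrees, SD 8.5, 50 per arm, power 90%, alpha 5%, DLL visits at 0, 1, 6 and 12 months. **Assumed here:** equal correlation rho between visits (0.5, range 0.3 to 0.7) and the patterns of true deficit below.

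**1. The plan's own figure.** n per arm = 2 × SD² × (z_alpha + z_power)² / margin².
- One-sided 5%: 2 × 72.25 × (1.645 + 1.282)² / 25 = 49.5, so 50. This matches.
- One-sided 2.5%: 2 × 72.25 × (1.960 + 1.282)² / 25 = 60.7, so 61. This does not match.

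The formula is for two means at one time point, with no repeated measures.

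**2. Direct 12-month contrast.** SE = 8.5 × √(2/50) = 1.70 degrees. Power is Φ(5/1.70 − 1.645) = 90.3% at one-sided 5% and Φ(5/1.70 − 1.960) = 83.7% at one-sided 2.5% (83.0% with the t distribution). Power to detect a 5-degree deficit at two-sided 5% is therefore about 83%.

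**3. Group main effect.** The estimate is the mean deficit over k visits, with SE = 1.70 × √((1 + (k − 1)rho)/k). At rho 0.5 this is 1.34 for four visits and 1.39 for the three postoperative visits.

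**4. Interaction.** Noncentrality = (n/2) × Σ(d_j − mean d)² / (SD² × (1 − rho)), where d_j is the true deficit at visit j. For 5 degrees at one visit out of four, this is 25 × 18.75 / 36.125 = 12.98 on 3 df.

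Power at rho 0.5, two-sided 5%:

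| True deficit at 0/1/6/12 months | Main effect, 4 visits | Main effect, 3 postoperative visits | Interaction, 4 visits | Direct 12-month contrast |
|---|---|---|---|---|
| 0/0/0/5 | 1.25 degrees, 15% | 1.67 degrees, 22% | 87% | 83% |
| 0/2/4/5 | 2.75 degrees, 53% | 3.67 degrees, 75% | 76% | 83% |
| 0/5/5/5 | 3.75 degrees, 79% | 5.00 degrees, 95% | 87% | 83% |
| 0/5/0/0 | 1.25 degrees, 15% | 1.67 degrees, 22% | 87% | 5% (no true difference) |

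Rows 1 and 4 have the same noncentrality, so the interaction cannot tell a 12-month deficit from a 1-month one. A simulation of 4,000 trials gave 0.877 for this pattern; the formula gives 0.87. For 0/0/0/5, rho 0.3 and 0.7 give main-effect power of 19% and 13% (four visits) and interaction power of 72% and 98%. If baseline is not a level of the time factor, a constant postoperative deficit has noncentrality 0 and the interaction stays at its 5% level.

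**5. Two outcome wordings.** If 8.5 is the SD of the 12-month value, the change score has SD 8.5 × √(2(1 − rho)) and the baseline-adjusted comparison has SD 8.5 × √(1 − rho²). Power at 50 per arm:

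| rho | Change score, one-sided 5% | Adjusted, one-sided 5% | Adjusted, one-sided 2.5% |
|---|---|---|---|
| 0.3 | SD 10.06, 80.0% | SD 8.11, 92.5% | 86.9% |
| 0.5 | SD 8.50, 90.3% | SD 7.36, 96.0% | 92.5% |
| 0.7 | SD 6.58, 98.4% | SD 6.07, 99.3% | 98.5% |

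The unadjusted 12-month comparison has 90.3% and 83.7% on the same two scales. If 8.5 is instead the SD of the change, the change score has the planned 90.3%.

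**The case against.** The best reply is that the plan does aim to compare the arms during follow-up, and that a group-by-time model, or its mixed or GEE replacement, holds the 12-month contrast in its fitted means. That stands. A reader might infer that the planned analysis cannot estimate the primary contrast, but the text does not support that. It leaves the contrast unnamed and does not make it primary.

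A reader might also infer that baseline is ignored, or that the comparison is biased for want of adjustment. Neither follows. The tests against baseline suggest that baseline may be a level of the time factor. The 12-month group-by-time contrast would then be the difference in change, which is what the Primary outcome section describes. No covariate is named, but an analysis plan that is not shown could name one, and in a randomised comparison its absence costs precision only.

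Nor is 15% the power of the planned analysis. It belongs to one of two tests under one pattern. The interaction has 76 to 87% power for the 12-month deficits shown, and the postoperative main effect reaches 95% when the deficit is constant. Similarly, 80% for a change score is the low end of a range, and applies only if 8.5 is the SD of the value.

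Finally, the two outcome wordings have the same expected between-arm difference under randomisation; only precision differs. That is a smaller point than the unnamed contrast.

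What survives is not mere silence of a condensed article. The section names a method and its follow-up comparisons, and these do not match the outcome and the sample size in the same article.

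**Conclusion.** The point holds in this form: the article defines and sizes the trial on one between-arm contrast at 12 months, then describes an analysis in which that contrast is not identified as the primary test. The outcome is also worded both as a value and as a change, with an SD tied to neither.

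The size depends on which ANOVA result is read as primary. For a deficit equal to the whole margin at 12 months, power runs from about 15% (four-visit main effect, deficit at 12 months only) to about 95% (postoperative main effect, constant deficit), against about 83% for the direct contrast. A 1-month difference alone makes the interaction significant in about 87 to 88% of trials with no 12-month difference. These figures rest on SD 8.5, 50 analysed per arm, equal visit correlation of 0.5 and the stated patterns. The correlation and the patterns are assumptions. The mismatch does not depend on them.

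The sample size is not shown to be wrong: it reproduces at one-sided 5%. Naming the contrast is essential because the main conclusion depends on it. Adjusting for baseline is worthwhile but secondary.

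**What to change.** State one primary estimand: the between-arm difference in mean 12-month DLL, in degrees, adjusted for preoperative DLL. Estimate it by ANCOVA, or as the 12-month contrast of a mixed model with treatment-by-visit terms and baseline DLL as covariate. Compare its confidence interval with the 5-degree margin at a stated one-sided alpha; the 50 per arm correspond to one-sided 5%. Word the outcome the same way in the abstract, the aim and the outcome section, and say which quantity the SD of 8.5 describes. Keep the 1- and 6-month contrasts, the overall profile and the comparisons with baseline as secondary.

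The cost is a few sentences. DLL is already measured at all four visits, so no patients, visits or data are added. The adjustment gains precision: from 90.3% to 92.5–96.0% power at one-sided 5%, or from 83.7% to 86.9–92.5% at one-sided 2.5%, for correlations of 0.3 to 0.5 if 8.5 is the SD of the 12-month value.

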**Figure 1 F1:**
[figure not shown]
Jamar E-Z Read Goniometer 12/32 cm.

To obtain a more precise and less variable measurement, before performing the test, three colored dots will be applied to the hip and ankle of the patients and on the underlying surface. During the test, a picture of the patient will be shot at maximum leg rise. Using the dots as reference points, the angle will be measured with computer software directly on the picture.

After measuring the angle, a score will be assigned for the calculation of AWS (5 points).

B. The test will be performed preoperatively and at 1 month, 6 months and 12 months postoperatively.

•41° or more (normal) 5 points

•31°-40° (good) 4 points

•21°- 30° (fair) 3 points

•11°-20° (poor) 2 points

•0°-10° (trace) 1 point

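### The primary comparison does not adjust for preoperative DLL, so a valid analysis gives up precision that data already collected would supply

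*Protocol article*

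**What the plan says.** - **Design.** "LABOR is a randomized, controlled, non-inferiority trial" (Design). The margin and spread are given together: the limit "will be set to 5 degrees with a standard deviation of 8.5 degrees" (Sample size calculation, randomization and statistical analysis). The same paragraph asks for 50 patients per arm, for 90% power at an alpha of 5%, without saying whether alpha is one- or two-sided.
- **Model.** "ANOVA for repeated measures will be adopted using DLL as the dependent variable" (same section). A rank transformation is held in reserve, and linear mixed or GEE models replace the ANOVA if many values are missing. No covariate is named for any of these. Baseline appears in the analysis text only as a time point that is compared with each follow-up visit under a Bonferroni correction. A p-value "lower than 0.05 will be considered statistically significant", again without sidedness.
- **Outcome.** The Primary outcome section has "Changes in baseline DLL measures at 12 months postoperatively in both groups". The Abstract (Methods and design) instead describes the difference in strength measured by DLL at 12 months.
- **Data.** For DLL, "The test will be performed preoperatively and at 1 month, 6 months and 12 months postoperatively" (double leg-lowering test section). The Abstract says that all participants have the preoperative strength assessment.

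**The concern.** Each patient contributes a preoperative DLL, but the model does not use it as a covariate. If baseline is one of the repeated levels, the 12-month contrast between arms is a change-score comparison, which fixes the weight on baseline at one. If baseline is left out of the repeated levels, the contrast compares raw 12-month values, which fixes that weight at zero. Adjustment lets the data choose the weight.

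What is at stake is the width of the confidence interval for the 12-month difference. In a non-inferiority trial that width largely decides whether a 5-degree loss can be excluded.

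**Working it through.** **Inputs from the article.** Margin 5 degrees, SD 8.5 degrees, 50 per arm, alpha 5%, power 90%. **Assumed.** True difference 0; equal SDs at baseline and 12 months; r = 0.3, 0.5 and 0.7, because no correlation is given; untransformed DLL.

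**1. Reproduce the stated size.** n per arm = 2 × 8.5² × (z_alpha + z_power)² / 5².
- One-sided 5%: 144.5 × (1.645 + 1.282)² / 25 = 49.5, so 50. This is the stated figure. With n = 50, SE = 8.5 × √(2/50) = 1.70, and power = Φ(5/1.70 − 1.645) = 90.3%.
- Two-sided 5%: 144.5 × (1.960 + 1.282)² / 25 = 60.7, so 61. With n = 50, power = Φ(5/1.70 − 1.960) = 83.7%.

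**2. Precision of the three comparisons.** Let s be the SD at each visit.
- Raw 12-month value: s.
- Change: s√(2(1 − r)).
- Baseline-adjusted: s√(1 − r²).

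The adjusted variance is therefore (1 − r²) times the raw variance and (1 + r)/2 times the change variance. Both factors are below 1 for 0 < r < 1. If the SDs differ (s0 at baseline, s1 at 12 months), the change variance exceeds the adjusted variance by (s0 − r·s1)², which is never negative. Adjustment is then never worse, and it ties with change only when s0 = r·s1.

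**3. Power with 50 per arm if 8.5 is the SD of the 12-month value.** Each cell gives one-sided 5% / two-sided 5%.

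| r | Raw | Change | Adjusted |
|---|---|---|---|
| 0.3 | 90.3 / 83.7% | 80.0 / 70.0% | 92.5 / 86.9% |
| 0.5 | 90.3 / 83.7% | 90.3 / 83.7% | 96.0 / 92.5% |
| 0.7 | 90.3 / 83.7% | 98.4 / 96.7% | 99.3 / 98.5% |

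Example: at r = 0.5 the adjusted SD is 8.5 × √0.75 = 7.36, SE = 1.47, and Φ(5/1.47 − 1.645) = 96.0%.

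**4. Power with 50 per arm if 8.5 is the SD of the change.** The adjusted SD is 8.5√((1 + r)/2), that is 6.85, 7.36 and 7.84.

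| r | Change | Adjusted |
|---|---|---|
| 0.3 | 90.3 / 83.7% | 97.7 / 95.4% |
| 0.5 | 90.3 / 83.7% | 96.0 / 92.5% |
| 0.7 | 90.3 / 83.7% | 93.9 / 89.1% |

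**5. In patients, at r = 0.5.** The n per arm for 90% power falls from 50 to 38 (49.5 × 0.75 = 37.1) at one-sided 5%, and from 61 to 46 (60.7 × 0.75 = 45.5) at two-sided 5%.

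**6. Simulation.** 20,000 runs with t-tests, 8.5 as the SD at every visit, one-sided 5%, and the covariate's degree of freedom counted. At r = 0.3, 0.5 and 0.7, adjusted power was 92.0%, 95.7% and 99.2%. Change gave 79.9%, 89.5% and 98.3%, and raw about 90%. The formulas are slightly optimistic, but the ordering stands.

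**The case against.** **Covariates belong in the analysis plan.** The article is condensed, and a separate plan may add the baseline term. That is fair. But the article does not merely stay silent: it names the model, names its dependent variable, and gives baseline the role of a time point. The comment addresses that stated choice.

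**Baseline is already used.** This also stands in part. With change as the defined primary outcome, the change score is the main comparator and the raw column matters less. Against change, the gain in step 3 is large when r is low and nearly vanishes at 0.7. In step 4 it also shrinks as r rises.

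**The size is unknown.** Correct. The correlation, the sidedness and the meaning of 8.5 are all open. If ranks are used, the figures do not apply directly. The direction of the gain in step 2 does not depend on sidedness or on the meaning of 8.5.

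**Stronger readings that a reader might infer, and that the documents do not support:**
- *The trial is underpowered and adjustment is the cure.* The stated 50 per arm reaches 90.3% at one-sided 5% before any adjustment. The shortfall to 83.7% appears only if alpha is two-sided, which the article does not say.
- *The planned analysis is biased.* It is not. Randomization makes both the raw and the change comparison valid. Adjustment only removes the effect of a chance baseline difference in the realised trial. For example, with SD 8.5 at both visits and r = 0.5, a baseline difference of one SE (1.70 degrees) moves either estimate by 0.5 × 1.70 = 0.85 degrees.
- *Baseline must predict 12-month DLL well because strength varies with age.* The Participants section says that the age cutoff is meant to minimize age-related differences in strength. It says nothing about the correlation between visits.
- *Small centres make imbalance likely.* The comparison is over about 100 patients, so the count per centre says little about overall imbalance.

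**Conclusion.** The point holds as a missed gain in efficiency, not as an error that invalidates the analysis. For 0 < r < 1 and equal SDs at the two visits, adjusting for preoperative DLL is more precise than either comparison that the stated model implies.

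At one-sided 5% and r from 0.3 to 0.7, the gain over the change score runs from about 1 percentage point (98.4% to 99.3%) to 12.5 points (80.0% to 92.5%) if 8.5 is the SD of the 12-month value. It runs from 3.6 to 7.4 points if 8.5 is the SD of the change. The gain matters most if p < 0.05 is meant as two-sided: at r = 0.5 adjustment would then bring power from 83.7% to 92.5%, above the planned 90%.

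Confidence is high for the direction. The size is conditional on the assumptions listed in the working. The change should be made, but the trial's conclusions would not be unsound without it.

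**What to change.** Replace the model statement for DLL with this: DLL at 1, 6 and 12 months as the repeated outcome, with group, visit, group-by-visit, baseline DLL and baseline-by-visit as terms. Take the adjusted 12-month difference between arms, with its confidence interval, in degrees, and compare it with the 5-degree margin. With baseline as covariate, the between-arm estimate is the same whether the endpoint is called the change or the 12-month value, so the difference in wording between the Abstract and the Primary outcome section no longer affects the result.

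Keep the planned baseline-versus-follow-up comparisons as a separate descriptive analysis. Treat the secondary outcomes that have a preoperative value in the same way, each with its own baseline (for example TR, AWS, SF-36, spirometry and CT volumetry).

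The cost is one degree of freedom per baseline term and a revised model statement. No further data or patients are needed, and the plan already names linear mixed models as its fallback. The change should be fixed before the arms are compared, so that the covariate cannot appear to have been chosen after seeing the result.

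### Rank-transforming DLL leaves no stated way to compare the primary result with a non-inferiority margin set in degrees

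*Protocol article*

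**What the plan says.** All references are to the protocol article.

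- **Design:** "LABOR is a randomized, controlled, non-inferiority trial".
- **Sample size calculation, randomization and statistical analysis (margin and size):** "the minimum DLL to define the non-inferiority of laparoscopic bridging vs. anatomic open reconstruction will be set to 5 degrees". The SD is taken to be 8.5 degrees. With 90% power and a 5% alpha whose sidedness is not stated, this leads to 50 patients per arm.
- **Primary outcome** and **Performance and measures: double leg-lowering test:** the endpoint is the 12-month change from baseline in DLL. DLL is an angle, read with a goniometer marked in 1-degree steps and also measured by software on a photograph. It is cut into 1 to 5 points only to build the abdominal wall strength (AWS) score.
- **Sample size calculation, randomization and statistical analysis (analysis):** DLL is the dependent variable in a repeated-measures ANOVA. Then: "Because the DLL test cannot have a normal distribution, a ranking transformation will eventually be used". The next sentence extends the approach to the other ordinal outcomes, naming pain VAS and the AWS score. The only decision threshold is a p-value below 0.05.

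**The concern.** A non-inferiority margin works only if the analysis yields an effect estimate, with its uncertainty, on the scale of the margin. Here the margin is a difference in degrees. An ANOVA on ranked DLL estimates differences in mean ranks. The article gives no back-transformation, no ranking after shifting one arm by the margin, and no confidence interval in degrees.

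The reason offered does not require ranking either. DLL is a measured angle, not an ordinal score. With about 50 patients per arm, a mean difference and its confidence interval do not need normally distributed individual values.

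If the transformation is applied as written, the primary analysis does not address the 5-degree question for which the trial was sized. If it is optional, the scale of the primary analysis stays open until the data have been seen, because no trigger is stated.

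**Working it through.** **1. Reproduce the sample size.** Inputs from the sample size section: margin 5 degrees, SD 8.5 degrees, power 90%, alpha 5%. Assumption: true difference zero.

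n per arm = 2 × SD² × (z_alpha + z_power)² / margin²

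- One-sided 5%: 2 × 72.25 × (1.645 + 1.282)² / 25 = 144.5 × 8.567 / 25 = 49.5, so **50 per arm**, as stated. Power at 50 per arm is 90.3%.
- One-sided 2.5%: 144.5 × (1.960 + 1.282)² / 25 = 60.8, so 61 per arm, which is not the stated figure.

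The plan's number is therefore a comparison of mean angles in degrees at one-sided 5%. The arithmetic is sound, and the stated power belongs to that test.

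**2. Try to carry 5 degrees to the rank scale.** For normal data with a shift of 5 degrees, the probability that a patient in the better arm exceeds one in the other arm is P = Φ(5 / (SD × √2)). With 50 per arm the expected difference in mean ranks is 100 × (P − 0.5).

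| SD (degrees) | P | Mean-rank difference equal to 5 degrees |
|---|---|---|
| 6 (assumed) | 0.722 | 22.2 |
| 8.5 (stated) | 0.661 | 16.1 |
| 12 (assumed) | 0.616 | 11.6 |
| 15 (assumed) | 0.593 | 9.3 |

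The same 5 degrees corresponds to anything from 9.3 to 22.2 mean ranks over this range. A margin on ranks would move with the observed spread, so it cannot stand in for the fixed margin.

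**3. Is normality needed?** A simplified simulation compared two groups at one time point: 50 per arm, SD 8.5, 6,000 runs per setting, one-sided 5%. The skewed data were a shifted gamma with shape 1.5.

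| Data | Test | Power (true difference 0) | Type I error (bridging truly 5 degrees worse) |
|---|---|---|---|
| Normal | t-based, in degrees | 0.902 | 0.049 |
| Normal | Margin-shifted ranks | 0.891 | 0.050 |
| Skewed | t-based, in degrees | 0.896 | 0.051 |
| Skewed | Margin-shifted ranks | 0.975 | 0.055 |

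For margin-shifted ranks, 5 degrees are added to the bridging arm before ranking. The degree-scale comparison of means keeps its error rate and power under marked skewness. This was not the full repeated-measures model.

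**The case against.** **The transformation may be conditional.** The article first names DLL itself as the dependent variable, and 'eventually' can be read as 'if needed'. This stands, so it would be wrong to say that the trial will certainly be analysed on ranks. But the stated reason, that DLL cannot be normal, makes ranking a likely path, and no trigger is given.

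**Ranks and margins can be combined.** A reader might infer that ranking makes it impossible to declare or refute non-inferiority, or that power must be lost. The documents do not support that. A Hodges-Lehmann interval or margin-shifted ranks keep the degree scale, and the latter had power of about 0.89 with normal data. The fair charge is that no such link is stated. An analysis plan that is not shown might supply one, but the published sentence would still conflict with the published margin.

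**The accept-the-null problem is not caused by ranking.** A reader might infer that this one sentence undoes the whole primary conclusion. It does not. The article gives only a p-value threshold, and both the abstract's Discussion and the Clinical implications section treat no difference as acceptance of the null hypothesis. If non-significance at two-sided 5% were read as success when bridging is truly 5 degrees worse, it would pass in about 19% of simulated trials on ranks (normal data). It would also pass in about 16% on unranked degrees (1 − 0.837, the two-sided power at 50 per arm). The missing non-inferiority decision rule is a separate defect, and deleting the ranking sentence does not cure it.

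**Interaction.** One might add that ranked ANOVA handles group-by-time interaction poorly. Nothing in the documents bears on this, and the primary outcome is the 12-month change, so the point does not rest on it.

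**Conclusion.** The point holds in limited form. The article provides for ranking the primary endpoint, perhaps only if needed, while its margin and sample size are in degrees, and no passage connects the two. Followed as written, a ranked repeated-measures ANOVA judged at p below 0.05 gives nothing to set against 5 degrees. This is a stated rule in conflict with the trial's own criterion, not merely a missing detail.

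The size of the problem is the mismatch itself. The 50 per arm and 90% power belong to a test of mean degrees, and the rank equivalent of the margin varies with the spread (16.1 at the stated SD, 11.6 at SD 12). These figures assume normal data, a true difference of zero for the sample size, and one-sided 5%, which the article does not state but which reproduces its number. The plan should be changed. The sample size calculation is not at fault.

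**What to change.** Remove the plain ranking transformation from the primary DLL analysis. State instead that the 12-month between-arm difference in DLL change will be estimated in degrees, adjusted for baseline, with a robust or bootstrap confidence interval if residuals are skewed. Compare its confidence limit with the 5-degree margin, at a level that matches the alpha used for the sample size (50 per arm corresponds to one-sided 5%).

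If a rank method is wanted, name one that keeps the degree scale, such as a Hodges-Lehmann interval or margin-shifted ranks, as a sensitivity analysis. Rank methods for the ordinal and VAS secondary outcomes can stay as planned.

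The cost is a short rewrite of the analysis paragraph and a little more analysis work. The number of patients and the measurements do not change. The change should be fixed before DLL results are compared by arm. The missing non-inferiority decision rule and the accept-the-null wording need their own correction.

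### The default repeated-measures ANOVA drops a whole patient for one missed DLL test, and the switch to another model has no stated trigger, so the primary method is not fixed in advance

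*Protocol article*

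**What the plan says.** All the analysis statements stand in the protocol article under Sample size calculation, randomization and statistical analysis.

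- Default method: "ANOVA for repeated measures will be adopted using DLL as the dependent variable".
- Change of method: "If a consistent number of missing values is detected during the follow-up, ANOVA for repeated measures will be replaced by linear mixed". The sentence continues with GEE models as the alternative.
- Reason given for the change: the replacement models "permit the exclusion of the data only from a single missing observation and not from the patient on overall as with ANOVA".
- Analysis set: "All analyses will be performed on an intention-to-treat basis".
- Numbers: 50 patients per arm, raised from 100 to 110 in total for 10% dropout.

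Elsewhere, Design states that "LABOR is a randomized, controlled, non-inferiority trial". The primary outcome is "Changes in baseline DLL measures at 12 months postoperatively in both groups". On timing, the section on the DLL test says: "The test will be performed preoperatively and at 1 month, 6 months and 12 months postoperatively". That makes one baseline and three follow-up measurements.

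**The concern.** Two things do not fit together.

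First, the authors describe their default method as one that excludes a patient entirely for a single gap, and they also promise that every analysis follows intention-to-treat. Both hold only if nobody misses a test or the switch is made. In between, randomised patients are removed. Some of them have both values that the primary outcome needs and lack only an intermediate one.

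Second, the method for the primary outcome depends on how much is missing once follow-up is under way. The text gives no threshold, and it does not say which of the two replacements would be used. These are not interchangeable: a likelihood-based mixed model is valid when data are missing at random, whereas unweighted GEE generally needs data missing completely at random.

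At stake are the number of patients behind the non-inferiority comparison and the reader's assurance that its method was settled beforehand.

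**Working it through.** **Inputs from the protocol article.** Margin 5 degrees, SD 8.5 degrees, power 90%, alpha 5% (sidedness not stated), 50 per arm, 10% dropout, 110 in total, three follow-up DLL tests.

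**Assumptions, not in the documents.** A share m of DLL tests is missing independently at each follow-up visit. Baseline is complete; a missing baseline would make the change from baseline uncomputable under any method, so it is not charged to ANOVA.

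**Step 1: the plan's own figure.** With a true difference of 0, n per arm = 2 × (1.645 + 1.282)² × (8.5/5)² = 49.5, so 50. This matches the plan and shows that alpha is one-sided 5%. One-sided 2.5% would give 61. The stated 110 is close to 112, which is 100/0.9 rounded up to equal arms. The sample size is not in dispute here.

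**Step 2: patients kept.** ANOVA keeps 110 × (1 − m)³. An analysis of every 12-month value keeps 110 × (1 − m).

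**Step 3: power.** Power = Φ(5 / (8.5 × √(2/n)) − 1.645), with n per arm half the number kept. For m = 5% under ANOVA, n = 94.3/2 = 47.15, and 5/(8.5 × √(2/47.15)) = 2.856. Then 2.856 − 1.645 = 1.211, which gives 88.7%.

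| Assumed m | (1 − m)³ | Kept by ANOVA | Power | Kept with 12-month value | Power |
|---|---|---|---|---|---|
| 3% | 0.913 | 100.4 | 90.4% | 106.7 | 91.8% |
| 5% | 0.857 | 94.3 | 88.7% | 104.5 | 91.3% |
| 8% | 0.779 | 85.7 | 85.9% | 101.2 | 90.6% |
| 10% | 0.729 | 80.2 | 83.9% | 99.0 | 90.0% |

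These powers apply the plan's own two-group formula to the patients retained. They show the effect of the numbers lost and nothing else; a model that uses the correlation between visits would have somewhat different power.

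**Step 4: when the allowance is used up.** The 10% allowance covers 110 − 100 = 10 patients. Whole-patient deletion uses it at m = 1 − (100/110)^(1/3) = 3.1% per follow-up visit.

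**Step 5: the opposite pattern.** If all missing data come from permanent dropout totalling 10%, then 110 × 0.9 = 99 patients remain under either approach and power is 90.0%. The cost of ANOVA therefore comes from intermittent missed visits.

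**The case against.** The best defence is that the protocol sees the problem and supplies the remedy in the same sentence. The conflict with intention-to-treat exists only below the trigger, and at the larger losses in the table the fallback would probably apply. A threshold and a model choice can also be set in a separate analysis plan, and this is a condensed article. This limits the size of the point but does not remove it: the article states a complete-case default and a switch that follows observed missingness, and deletion continues until that switch is made.

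A reader might go further in three ways that the documents do not support.

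- *Deletion biases the result towards no difference.* This assumes who is missing and from which arm. The documents say neither, so the direction is unknown.
- *The open choice allows a favourable result to be picked.* The trigger is the amount of missing data, not the treatment effect, and the analysis is given to a statistician who does not collect the data. There is discretion, but nothing shows selection on results.
- *The loss of power is severe.* Larger figures come from counting the baseline test against ANOVA alone, or from charging it with the expected dropout, which reduces any 12-month analysis. With 10% dropout plus 5% missed visits, the available 12-month values number 110 × 0.9 × 0.95 = 94 (88.7%), against 110 × 0.9 × 0.857 = 85 (about 86%) under ANOVA.

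**Conclusion.** The point holds at moderate size. The default analysis conflicts with the intention-to-treat statement whenever the fallback is not used, and it can discard patients whose primary outcome is fully observed. Because the trigger is unquantified and the replacement is one of two models, the primary method is not fixed in advance. Both defects are in the wording and do not depend on any missing rate.

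The numerical cost does depend on one, and the documents give none. At an assumed 3–5% missing per follow-up visit, ANOVA deletes about 9–14% of the 110 patients. That costs about 1.4 to 2.6 points of power compared with using all 12-month values. At an assumed 10% per visit the gap is about 84% against 90%, if ANOVA were still kept at that level of loss. With permanent dropout alone there is no penalty.

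**What to change.** Name one likelihood-based linear mixed model as the primary analysis of DLL, whatever the amount of missing data. It should model DLL in degrees, so that the estimate can be set against the 5-degree margin, with treatment by visit and baseline DLL. The treatment contrast at 12 months should be the primary comparison. Delete the conditional switch, and delete the GEE alternative for the primary outcome. Add one sensitivity analysis for missing 12-month values under less favourable assumptions. The covariance structure and the exact form of the sensitivity analysis are for the trial statistician to choose, provided they are written down before the data are seen.

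The cost is a change of analysis wording and one extra sensitivity analysis. The protocol already lists linear mixed models, and no patient, visit or measurement is added.
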